## Abstract

**Background:**

The transdiagnostic symptom of anhedonia, or the loss of pleasure in previously pleasurable things, is common across several chronic physical and mental illnesses. Music therapy has been effective in treating a range of conditions associated with anhedonia, but only 3 cases have been reported that targeted increasing hedonic capacity and all relied on descriptive data (qualitative and quantitative). Functional magnetic resonance imaging (fMRI) evidence demonstrates that pleasure is associated with increased activity in the limbic system, including the anterior cingulate cortex, as well as the prefrontal cortex. As such, changes within these regions may provide objective evidence to explore how music therapy acts to reduce anhedonia symptomatology.

**Objective:**

Our primary aim is to examine the feasibility of a music therapy intervention to increase hedonic capacity among individuals with anhedonia. We also aim to examine congruence across psychometric results and interview data to generate estimates of effect size and explore participants’ qualitative experiences. In addition, we aim to identify any correspondence between these outcomes and changes in brain activity associated with reward processing during targeted fMRI tasks. This study will generate hypotheses for testing in future studies.

**Methods:**

This pilot study uses a sequential mixed methods design to first identify whether there are pre-post changes in the primary outcome measures and then to identify correlations between interview data, psychometric data, and objective measures of brain structure and functioning (fMRI). Participants were 13 adults with high cognitive function who scored within the clinical range for anhedonia on the Dimensional Anhedonia Rating Scale (DARS). Participants were engaged in a 4-month music therapy intervention developed through preliminary case studies, which involved daily independent pleasure-focused music activities and regular contact with a therapeutic guide. The fMRI data acquired include resting-state fMRI and task-based functional paradigms designed to probe musical pleasure (music listening task) and reward prediction (reversal reward learning task). Data will be analyzed using individual general linear models to identify associations with symptom improvement, as well as longitudinal changes in functioning.

**Results:**

The study received internal funding support from the University of Melbourne in September 2024. Data collection commenced in August 2025 and was concluded by mid-2026. As of September 2026, 13 participants have been recruited, and data will be analyzed by the end of 2026, with results expected to be published in 2027.

**Conclusions:**

The results of this pilot study will contribute to knowledge about the effects of this music therapy intervention on reducing anhedonia and introduce a study protocol that could be used in subsequent, more robust studies to explore potential mechanisms.

## Introduction

### Background

Anhedonia has been recognized as a transdiagnostic symptom associated with a range of chronic illnesses [1]. It is defined as “markedly diminished interest or pleasure in all, or almost all, activities” [2] and is often accompanied by a lack of motivation or engagement and diminished decision-making capacity. Although it is a core symptom of major depressive disorder (MDD), it is also associated with schizophrenia, substance use disorder, posttraumatic stress disorder, as well as neurological conditions such as Parkinson disease, traumatic brain injury, and chronic pain [3-5]. Importantly, anhedonia symptoms are both clinically underrecognized [6] and respond poorly to conventional antidepressant treatments [7,8], highlighting an unmet need for effective interventions. Regarding psychological interventions, positive affect treatments that increase reward sensitivity are superior to those focusing on negative affect [9] and show some potential for novel treatments such as those using music.

A range of studies have shown music therapy to be effective in increasing positive affect in the above illnesses. For example, a Cochrane review of music therapy for people with schizophrenia [10] found a positive effect on global state and negative symptoms (which align with positive affect treatments). Another Cochrane review of music therapy for depression [11] found improvements in depression, anxiety, and daily functioning, and improvements in anxiety and depression were also demonstrated in a Cochrane review of patients with cancer [12]. A more recent systematic review of music therapy in Parkinson disease [13] suggested emotional and motivational improvements that may be related to anhedonia but were not specified as such. Similarly, a Cochrane review of music therapy for substance use disorders [14] identified a moderate effect on motivation for treatment or change when compared to standard care. Additional systematic reviews of music therapy demonstrate reasonably consistent effects on transdiagnostic symptoms such as anxiety [15], depression, and quality of life [16]. However, there is little understanding of the mechanisms underpinning music therapy interventions [17]. Anhedonia may be another transdiagnostic symptom worthy of investigation.

Music therapy has been described as a complex intervention that requires contextual sensitivity [18]. Complex interventions, however, do not typically operate via a single causal mechanism; instead, they involve a mixture of biophysiological, neuropsychological, and sociobehavioral mechanisms of action, influenced by an interplay of therapeutic factors [19]. Flow has been proposed as 1 possible neuropsychological mechanism of change that provides a positive framing of music therapy [20] and may be consistent with the idea of positive affect treatments. Our previous case studies in anhedonia introduce another possibility: an increased focus on pleasure [21,22]. As such, an increase in pleasurable experiences through music therapy may improve positive affect (reward liking) as well as motivation (reward wanting). There is surprisingly little literature in music therapy on the topic of pleasure [23]. However, reviews are emerging based on qualitative reports [24] and brain imaging studies [25].

There is a rich body of literature documenting the use of functional neuroimaging to investigate neural correlates of music listening. This work began with electroencephalographic measures [26], which demonstrated the ability of music to modulate cortical rhythms but was limited by the low spatial resolution of the technique. Throughout the 1990s, positron emission tomography (PET) imaging became the primary modality and was beneficial because of its ability to localize neural responses to cerebral regions. One landmark PET imaging study [27] found spontaneous activation (inferred from cerebral perfusion, which was visualized by an oxygen-15 radiotracer) of the limbic and paralimbic systems while passively listening to unfamiliar but reportedly “pleasurable” instrumental music. Specific areas of activation included the subcallosal cingulate gyrus, anterior cingulate cortex, hippocampus, anterior insula, and nucleus accumbens. These findings have been frequently replicated and expanded upon since the development of blood oxygenation level–dependent (BOLD) functional magnetic resonance imaging (fMRI) [28-31], which has identified further activations (particularly in response to specifically “pleasurable” music) in the inferior frontal gyrus, ventral striatum, and Rolandic operculum, for example. Comprehensive investigations of pleasure have identified an evolutionarily conserved hedonic network encompassing the ventral pallidum, nucleus accumbens, insula, and ventromedial prefrontal cortex [32,33]. Meta-analytic fMRI studies further demonstrate modality-specific representations, with the insula playing a key role in representing pleasure induced by music [33].

These findings about pleasure-induced responses are further supported by results in clinical populations. For example, 1 study [34] investigated the neural response to passive listening to personalized “neutral” and “enjoyable” music in 16 patients with MDD, compared to 15 controls. Both groups demonstrated greater BOLD activation in the medial orbitofrontal cortex and nucleus accumbens while listening to “enjoyable” compared to “neutral” music, with controls showing a higher magnitude of activation difference than patients in the medial orbitofrontal cortex. Similarly, reduced activation in the anterior cingulate cortex in response to pleasurable music and positive emotional face presentation was identified in a study investigating patients with remitted depression compared to matched controls [35].

These findings are informative but not fully representative of an anhedonia-specific investigative lens. Despite the vast array of fMRI studies focused on depression, there is limited research into anhedonia specifically. The existing literature has mainly used in-scanner reward tasks to probe functional activation and has identified correlations between anhedonia severity and ventral striatum or amygdala hypoactivity [36,37] and ventromedial prefrontal cortex hyperactivity [37]. A greater breadth of studies has investigated task-induced reward “wanting” and “liking” in MDD without specific correlation with reported anhedonia severity. These have reported increased recruitment of the paralimbic anterior cingulate cortex, dorsolateral prefrontal cortex, and medial prefrontal cortex during reward “wanting” and “liking” phases by patients [38,39], alongside hypoactivity of the limbic ventral striatum and nucleus accumbens, amygdala, and caudate, among others [7].

More recently, studies have focused on the specific concept of “musical anhedonia,” or the absence or reduction of pleasurable emotional arousal while listening to music [40,41]. People experiencing musical anhedonia have shown significant hypoactivity in the nucleus accumbens while listening to music, as well as decreased functional connectivity between the right superior temporal gyrus and the nucleus accumbens [42], evidencing disruptions in the connectivity of auditory sensory regions and the associated limbic structures that relate to the ability to generate the feeling of pleasure. This is a promising area of research but is distinct from the focus of this study, which is on general anhedonia with music as an intervention, and none of the participants reported changes specific to musical pleasure.

Despite the frequent occurrence of anhedonia associated with a range of chronic physical and mental illnesses, there is limited evidence of successful interventions. To date, only positive affect treatments have demonstrated repeated success [43], and the Craske model [9] informed the conceptualization of the music therapy intervention tested here, which includes the core features of regularity, daily practice, and cognitive attention to pleasurable sensations. To date, this music therapy intervention has resulted in measurable improvements in anhedonia symptoms (Dimensional Anhedonia Rating Scale [DARS]) for 3 case studies, as consolidated by interview data [21,22]. However, it is unclear whether these results will be repeated with a larger sample and whether further objective markers of improvement could be demonstrated. Therefore, pilot study data are needed to refine a focus on relevant dimensions of anhedonia that might be modified by a complex intervention such as music therapy through the exploration of objective measures of both anhedonia and pleasure. This manuscript serves as a published protocol for a pilot study and can be used in a subsequent study if findings indicate feasibility.

### Objectives

Our primary aim is to examine the feasibility of leveraging a music therapy intervention to increase hedonic capacity among individuals with anhedonia. We also aim to examine congruence across psychometric results and interview data to generate estimates of effect size and qualitative experience. In addition, we aim to identify any correspondence between these outcomes and changes in brain activity associated with reward processing during targeted fMRI tasks. This study will generate hypotheses for testing in future studies by investigating the following research questions (RQs):

RQ 1: To what extent is the music therapy intervention feasible, based on measures of participant adherence, engagement, and retention?RQ 2: Do overall changes in participant scores on psychometric measures of anhedonia from before to after the music therapy intervention correspond with patterns in descriptions of change in interviews?RQ 3: Are pre-post changes in activity across reward processing regions during fMRI tasks associated with changes in anhedonia symptoms?

### Study Design

Given the findings from previous case studies, a sequential mixed methods study design is suitable for use in this pre-post pilot study to explore congruences between psychometric, interview, and fMRI data regarding changes in hedonic capacity among individuals with anhedonia following the music therapy intervention. Neither a strictly explanatory nor exploratory model (according to Creswell and Plano [44] definitions) is used, but the design will prioritize quantitative data from psychometric scales and seek to understand any significant differences from before to after intervention using interview data collected after intervention. This will cautiously extend case study findings of the same music therapy intervention [21,22] to determine whether psychometric outcomes are significant at the group level, as well as to explore patterns in the interview data to better understand any changes on the 2 different outcome measures—the DARS [45] and the Snaith-Hamilton Pleasure Scale (SHAPS) [46]. It would be premature to include a control condition at this stage, and similarly, the sampling of participants will be restricted to high-functioning people with anhedonia to better understand the phenomenon before extending the research to more clinical populations, such as those with schizophrenia or MDD. In addition, the study will assess the feasibility of the intervention and study procedure to inform a subsequent larger-scale study [47]. Feasibility measures will evaluate the acceptability, adherence, and practicality of delivering the intervention in adults with high cognitive function, while preliminary estimates of intervention effects and variability will be used to inform sample size calculations and the design of a future fully powered study.

Several psychometric measures of anhedonia could be used to identify eligible participants for this study, with the DARS being most relevant because it includes a multidimensional focus on both anticipatory and consummatory pleasure that were measured in the previous case studies and appeared appropriate [21,22]. It has also demonstrated greater sensitivity to subtle differences in a German study of a similar cohort of young adults [48] and is more personalized, with participants listing chosen activities rather than having fixed items presented. By comparison, the SHAPS is more focused on consummatory pleasure [46] and has been widely validated in clinical populations (populations with schizophrenia, substance use, or depression) [49,50], which may be relevant for subsequent studies, making it useful for inclusion as a measure of change. Despite these differences, the DARS has strong convergent validity with the SHAPS in some research [51], and this may prove useful for exploring convergence with patterns from interview data, as well as correspondence with reward processing activity.

Subsequently, task-based fMRI data will be useful to explore whether activity in reward-related regions of the brain corresponds with changes in our outcomes of interest. These data will provide an estimate of effect size and identify key regions of interest to be explored in future studies.

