### Sample Size

A sample size of 13 was selected to provide adequate depth of qualitative data (interviews) while maintaining feasibility for resource-intensive fMRI data collection. This sample size is sufficient for exploratory mixed methods analysis and effect size estimation, although it is underpowered for statistical inference [53].

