### Data Analysis

Repeated-measures *t* tests will be conducted on pre-post DARS and SHAPS scores to examine directional change. Hedges *g* will be calculated to estimate effect sizes, which will inform power calculations for a future fully powered study. *P* values will be reported descriptively but not interpreted as indicators of statistical significance, given the small sample size (N=13).

fMRI data will be analyzed using individual general linear models to identify longitudinal changes associated with the intervention. For each task, blocked-design general linear model analyses will be specified at an individual participant level in Statistical Parametric Mapping version 12 (SPM12) to model specific conditions of interest. For the reward-reversal task, this will involve contrasting unexpected punishment trials with expected reward trials. For the music task, the primary contrast will compare pleasurable music with neutral music. Repeated-measures, flexible factorial designs (within-subject factors: primary contrast×time) will be used at the group level to examine longitudinal changes. These will then inform exploratory investigations of associations between these effects and symptom improvement.

Inductive thematic analysis will be used to identify patterns in descriptions of change and group similar ideas from across the interview data [58]. Labels will be selected that verifiably represent the participant quotes contained within each theme, and these will be checked by the research team as a form of peer debriefing to identify blind spots and adjusted when found to be dissimilar.

Sequential analysis will be conducted by comparing the themes from interviews to overall changes in participant scores on psychometric measures of anhedonia from preintervention to postintervention assessments to identify any correspondences. Themes will also be compared to any changes in activity across reward processing regions during reward fMRI tasks and targeted music listening evident from preintervention to postintervention assessments that correspond with patterns of congruence in the psychometric data.

Feasibility will be documented based on verbal feedback following fMRI data acquisition and in the final interview. Anything beyond individual preferences will be used to inform necessary changes to the protocol.

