### Limitations

The lack of a control group and the small sample size are limitations of the study design. A control group will be included in subsequent studies, once we have determined whether the intervention increases hedonic capacity among individuals with anhedonia and whether any congruences across psychometric results and interview data are identified. This pilot will also enable us to test whether the musical pleasure fMRI paradigm can produce results indicative of reward pathways in those with anhedonia. Nevertheless, it will remain challenging to blind both participants and researchers. The enhanced sensitivity and specificity of fMRI data acquired on the 7T MAGNETOM Plus MRI system may help mitigate the limitations associated with the small number of participants.

There will be some flexibility in the delivery of the intervention since therapeutic integrity is challenged by an overly fixed intervention manual that does not respond to presenting needs. We have published the music therapy intervention [22] that addresses validity and replicability by transparently outlining four categories of principles: (1) unique and essential, (2) essential but not unique, (3) acceptable but not necessary, and (4) not acceptable (proscribed), as recommended in previous music therapy studies [59]. This framework has been used in this study and in additional case studies.

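### Study Design promises a verdict on group-level significance that Data Analysis rules out, and Limitations credits an uncontrolled pilot with determining whether the intervention works

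*Protocol article*

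**What the plan says.** The protocol article describes the same pre-post comparison in different terms.

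- **Study Design** gives as a purpose "to determine whether psychometric outcomes are significant at the group level". It adds that the design will "seek to understand any significant differences from before to after intervention using interview data collected after intervention". The same section calls a control condition premature at this stage.
- **Sample Size** justifies 13 participants by qualitative depth and the demands of imaging, and accepts the number "although it is underpowered for statistical inference".
- **Data Analysis** states that repeated-measures t "tests will be conducted on pre-post DARS and SHAPS scores to examine directional change", that Hedges g will be calculated, and that P "values will be reported descriptively but not interpreted as indicators of statistical significance".
- **Limitations** concedes the missing control group and the small sample, then says a control group will come in later studies "once we have determined whether the intervention increases hedonic capacity among individuals with anhedonia".
- **Objectives** makes feasibility the primary aim and calls the study hypothesis-generating. **Outcomes** uses adherence and retention to judge whether a larger trial is supported, and the end of **Background** makes reuse of the protocol depend on feasibility.

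**The concern.** There are two faults, and both can be seen in the text.

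First, Study Design sets the pilot a task (deciding significance) that Data Analysis forbids and Sample Size says the study is too small for. A reader of the results could cite Study Design to report a low P value as a finding, or Data Analysis to set a high one aside. The Results section puts the analysis at the end of 2026, so the purpose should be settled before then. Background also offers this protocol for reuse in a later study, which would carry the conflict forward.

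Second, Limitations treats the pilot as able to determine whether the intervention raises hedonic capacity. Without a comparison group, a pre-post change combines any intervention effect with natural course, repeat testing, attention from the therapist and regression to the mean. The last is a live issue for the DARS, because a score below 44 is the entry rule (Eligibility Criteria) and the screening score is also the baseline (Outcomes). What is at stake is the claim the pilot may make, not the numbers it will compute.

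**Working it through.** **1. The passages side by side**

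| Question | One place | Another place |
|---|---|---|
| Will significance be judged? | Study Design: yes, at group level | Data Analysis: no, P values are descriptive only |
| Is N=13 enough for inference? | Study Design presupposes it | Sample Size: underpowered |
| What do interviews explain? | Study Design: significant differences | Data Analysis and RQ 2: overall changes in scores |
| What precedes a controlled study? | Limitations: having determined whether the intervention works | Outcomes and Background: feasibility |

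The first row is a direct contradiction about the same t tests on the same two scales.

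**2. What a significance reading at n=13 would deliver**

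The plan gives no alpha, sidedness, effect size or standard deviation, so it has no power figure to reproduce. Inputs:

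- From the plan: n = 13, one group, paired t test.
- Assumed: alpha 0.05, all 13 pairs complete, and a standardised change d equal to the mean change divided by the SD of the changes.

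Degrees of freedom = 13 − 1 = 12. The two-sided critical value is t(0.975, 12) = 2.179. The noncentrality parameter is d × √13 = 3.606 d. Power is the probability that a noncentral t with 12 degrees of freedom falls beyond the critical value.

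| True d | Noncentrality | Power, two-sided 0.05 | Power, one-sided 0.05 |
|---|---|---|---|
| 0.3 | 1.08 | 16.9% | 26.6% |
| 0.5 | 1.80 | 38.2% | 52.2% |
| 0.8 | 2.88 | 75.4% | 85.8% |

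The d needed for 80% power is 0.85 two-sided and 0.73 one-sided. The one-sided column is shown because the plan speaks of directional change without fixing the test's sidedness.

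The smallest observed d with two-sided P<0.05 is 2.179 / √13 = 0.60. At a true d of 0.5, non-significance would occur in 100 − 38.2 = 61.8% of such pilots.

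These figures agree with the plan's own description of the study as underpowered.

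**3. What estimation would deliver**

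The 95% confidence interval for the mean change has half-width 2.179 × SD / √13 = 0.60 SD of the changes. For an observed d of 0.5, inverting the noncentral t gives an interval of about −0.09 to 1.07. That is wide, but it states honestly what 13 pairs can show, and it serves the stated use of informing a later sample size.

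**4. Attribution**

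No arithmetic is needed. Whatever the P value, there is no concurrent comparison from which to subtract the change expected without the intervention. Estimating a pre-post change is within the design; determining that the intervention caused it is not.

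**The case against.** The strongest reply is that the operative text is already restrained. Data Analysis expressly bars the significance reading, Sample Size agrees, Objectives lists no significance aim, and Study Design itself speaks of extending the case studies cautiously and ends with preliminary estimates. Integration of the interviews is not conditional on P in Data Analysis or RQ 2, and Hedges g is already planned. Limitations openly names the missing control group. The power figures only quantify a shortfall that the plan admits.

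Most of this stands, and it limits the point to wording. It does not remove it. An explicit analysis rule does not cancel a stated purpose that contradicts it, and admitting the lack of a control group does not license the next sentence's claim to have determined an effect.

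Two stronger readings are tempting but unsupported:

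- A reader might infer that the controlled trial depends on a positive efficacy result instead of feasibility. The documents do not say so. Limitations says *whether*, not *that*, and sets no threshold. Outcomes and Background already tie progression to feasibility.
- A reader might want a false-positive rate from regression to the mean. The documents give neither the test-retest correlation of the DARS nor where 44 falls in the source population. Any such rate would reflect the assumptions chosen, so none is claimed here.

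**Conclusion.** The point holds as an internal contradiction plus one over-strong clause. Study Design's significance purpose cannot stand with Data Analysis and Sample Size. The Limitations clause claims a determination that an uncontrolled pre-post design cannot make, and it sits beside a different, feasibility-based route to the next study.

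The textual conflict rests on no assumption. Its scale rests on the assumed two-sided 0.05 level and 13 complete pairs: power of about 17%, 38% and 75% at standardised changes of 0.3, 0.5 and 0.8, with about 0.85 needed for 80%. A one-sided test would raise these figures, and dropout would lower them.

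Severity is minor to moderate. No test, estimate, sample size or data item is wrong on this account, but what the pilot may conclude should be fixed before the results are written.

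**What to change.** 1. **Study Design, purpose.** Replace the significance purpose with: *estimate the mean pre-post change and Hedges g on each scale, with 95% confidence intervals*. The intervals are the only addition to the planned analysis.
2. **Study Design, interviews.** Change the reference to significant differences to *any changes*, so that it matches Data Analysis and RQ 2 and interviews are used whatever the P value.
3. **Limitations.** Delete the clause "once we have determined whether the intervention increases hedonic capacity among individuals with anhedonia". Base the move to a controlled study on the feasibility results, as Outcomes already does. The rest of that sentence, on congruence between scales and interviews, can be kept as something the pilot will report.
4. **Limitations.** Add one sentence saying that a pre-post change in this study cannot be attributed to the intervention.

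The cost is a few lines of text and two confidence intervals per scale. The downside is that the stated claims become more modest.
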